#### *Cost-effectiveness analysis*

We will also determine the cost-effectiveness of the intervention compared with usual care. The conduct of the cost-effectiveness analysis will be from the adopter’s perspective, such as the state medical assistance programs or state quitline and tobacco control programs. From this viewpoint, costs are measured by the per participant budgetary costs incurred as a result of implementing the interventions. In practice, this cost concept is similar to that used in many existing cost-effectiveness analyses of smoking cessation programs. The costs to be considered are those related to proactive outreach (mailed invitation materials, telephone outreach), telephone counseling, free NRT, data keeping, materials and overhead. This program perspective does not include indirect costs incurred by individuals. The study also takes care to distinguish those data and processing costs related to the scientific evaluation of the intervention and those related to the intervention itself, and only include the latter in the cost-effectiveness analysis.

The analysis uses the difference in six-month prolonged abstinence as the effectiveness measure. Measures of effectiveness and costs are aggregated and incremental cost-effectiveness ratios (ICERs) will be constructed for the two arms. The ICER takes the form: (C_T_ – C_UC_)/(O_T_ – O_UC_) where (C_T_ – C_UC_) is the expected difference in the costs (C) between the treatment and usual care and (O_T_ –O_UC_) is the corresponding expected difference in the outcome of interest (O), namely the numbers of individuals achieving prolonged abstinence at 12 months. Such ratios can be thought of as measuring the price at which an added unit of the outcome can be purchased by replacing UC with the treatment. We will use bootstrap methods to estimate standard errors and confidence intervals for these cost-effectiveness measures. This approach provides a convenient, nonparametric means of incorporating the correlation of costs and outcomes into the resulting standard errors. Sources of uncertainty in the specification of components of the cost measures are addressed by employing probabilistic sensitivity analyses, where the distributions of the variables representing the analytical assumptions are allowed to vary simultaneously, thus testing the robustness of our findings [51]. This analysis is repeated for the different sets of sensitivity analyses described above. In these analyses the total costs of the intervention do not change but the effectiveness measures changes with the different assumptions.

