### Usual care comparison group

All MHCP enrollees are assigned a primary care provider and usual care participants are able to see their provider to access smoking cessation treatment. However, depending on the primary care provider’s willingness and capacity to adhere to guidelines, tobacco treatment is variable, ranging from brief advice and medications to intensive counseling. Usual care participants also have access to smoking cessation medications at substantially reduced cost because MHCP provides insurance coverage for all recommended first-line nicotine replacement products (patch, gum, lozenge, inhaler, and nasal spray), as well as sustained-release bupropion and varenicline. However, an enrollee must obtain a prescription from a provider. Enrollees who fill a prescription may have a co-payment of between $1-$5. Participants can also buy nicotine replacement products out-of-pocket, which are available over-the-counter (i.e., patch, gum, lozenge). Additionally, all residents of Minnesota can access free tobacco treatment counseling from the state quitline ([name]).

In sum, participants assigned to usual care are able to receive the same or similar smoking cessation treatment components (including pharmacotherapy and telephone counseling) as those given to participants in the proactive care intervention group. What differs is that participants in the proactive intervention are specifically invited – through the methods of proactive outreach -- to consider treatment for tobacco dependence, and given facilitated access to treatment options, whereas participants in the usual care intervention must self-initiate access to treatment.

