#### *Free NRT*

The study also provides a free 8-week course of NRT (patch, gum or lozenge), which is mailed directly to participants in anticipation of their quit date. The protocol is based on the US Public Health Service Guideline recommendations [29,30]. All participants who receive telephone counseling are offered NRT unless they have one of the following contraindications: 1) recent (within 2 weeks) heart attack or severe arrhythmia, 2) unstable angina, 3) pregnancy; or they decline medication. If participants are interested in other smoking cessation medications (e.g., bupropion, varenicline), they are referred to their primary care provider to obtain a prescription. Participants who relapse and attempt to quit again are able to receive an additional 4 weeks of NRT.

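### The listed costs are all proactive-program costs, so for a medical-assistance adopter the ICER is a program-cost ratio that omits MHCP-paid cessation medication

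*Protocol article*

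**What the plan says.** The Cost-effectiveness analysis section of the protocol article takes the viewpoint of an adopter, "such as the state medical assistance programs or state quitline and tobacco control programs". For that viewpoint, "costs are measured by the per participant budgetary costs incurred as a result of implementing the interventions". The components follow: "The costs to be considered are those related to proactive outreach", by mail and by telephone, and then counseling by telephone, the free NRT, data keeping, materials and overhead. Two exclusions are stated. One is the cost of the scientific evaluation. The other is given as "This program perspective does not include indirect costs incurred by individuals".

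The numerator of the ICER is C_T – C_UC, which "is the expected difference in the costs (C) between the treatment and usual care". The article reads the ratio as the price of one more unit of outcome when the treatment takes the place of usual care.

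Elsewhere, the Usual care comparison group section says that "MHCP provides insurance coverage for all recommended first-line nicotine replacement products", and also covers sustained-release bupropion and varenicline. A prescription is needed and the enrollee may pay $1 to $5. The Free NRT section says of proactive-arm participants who want a drug such as bupropion or varenicline that "they are referred to their primary care provider to obtain a prescription". The Outcomes section expects the outreach to lead some smokers to treatment outside the study, and plans to extract MHCP pharmacy claims, but as a utilization measure only.

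**The concern.** If the adopter is the medical assistance program, its budget already pays for cessation drugs under usual care, and it would go on paying for some of them under the proactive program. The amount may change in either direction. Free study NRT may replace NRT that MHCP would have bought, while outreach and provider referral may create bupropion or varenicline claims that would not otherwise have arisen.

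The numerator and denominator are also mismatched. Abstinence is counted at population level, whatever treatment the smoker used and whoever paid for it. A quit helped by MHCP-paid varenicline therefore counts as an outcome in its arm, while no listed item carries the cost of the drug.

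The Abstract places cost-effectiveness among the primary objectives and makes the case for national dissemination conditional on it. A medical assistance program reading the result would want its own incremental cost, and the listed items do not supply it.

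**Working it through.** The article gives no program cost, drug cost, ICER or threshold, so there is no planned figure to reproduce. The check is algebra on the stated ICER, followed by an illustration.

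**Which arm each listed item belongs to.** Mailed invitations, telephone outreach, telephone counseling, free NRT, data keeping, materials and overhead are all parts of the proactive program as described under Proactive care intervention. None is identified as a usual-care cost.

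**Notation, per randomised participant**
- P: program cost in the proactive arm (not given)
- m: MHCP-paid medication cost per user (not given)
- u_T and u_UC: shares of each arm using MHCP-paid medication (not given)
- d: difference in six-month prolonged abstinence. The illustration uses 0.035 and 0.04, the differences in the Sample size and power analysis section.

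**Formulas**
- Listed items only: C_T = P, nothing enters C_UC, so ICER = P/d.
- Medical-assistance payer: ICER = [P + m(u_T – u_UC)]/d.
- Discrepancy: m(u_T – u_UC)/d in dollars, or m(u_T – u_UC)/P as a share of the listed-items ICER.

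The discrepancy vanishes only if net MHCP medication spending is equal in the two arms. That is doubtful as a default, because changing treatment utilization is itself an objective of the trial.

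**Sensitivity per $10 of net omitted cost**
- d = 0.035: $10/0.035 = $286 per added quitter
- d = 0.04: $10/0.04 = $250 per added quitter

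**Illustration.** P = $100, m = $300 and the uptake figures are assumptions; d = 0.04. The listed-items ICER is $100/0.04 = $2,500.

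| u_T | u_UC | Net omitted cost | Payer ICER | Change |
|---|---|---|---|---|
| 15% | 25% | $300 × (–0.10) = –$30 | $70/0.04 = $1,750 | –30% |
| 20% | 20% | $0 | $100/0.04 = $2,500 | 0% |
| 25% | 15% | $300 × 0.10 = +$30 | $130/0.04 = $3,250 | +30% |

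Over P = $50 to $200, m = $100 to $300 and uptake differences of –10 to +10 points, the change runs from –60% to +60%. The extremes come from one corner of that assumed grid ($30/$50 = 60%), and the range includes zero.

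**Whether the planned sensitivity analyses cover it.** The probabilistic analysis varies assumptions about components of the cost measures, and an item that is not a component is not varied. The repeats under different nonresponse assumptions hold total intervention cost fixed and change only effectiveness.

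**The case against.** The strongest reply is that the section is consistent on its own terms. The viewpoint is an adopter's, and the text also calls it a program perspective. Cost is defined as what implementing the interventions adds to a budget, and the article notes that many cessation analyses cost programs in a similar way. On that reading the question is what an organisation pays to run the program per added quitter, and the list answers it. This stands as a defence of the program-cost ratio as a legitimate measure. It does not make that ratio the incremental cost of a medical assistance program, which is the first adopter named.

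A reader might infer that the analysis is committed to the state payer's perspective. It is not: the payer is one example, offered as an alternative to quitline and tobacco control programs. A reader might also infer that the plan sets usual-care cost to zero. No sentence does so, and C_UC remains in the formula; what can be said is that none of the listed components fills it. MHCP claims are not expressly excluded either, and prescriptions prompted by referral could be argued to result from implementation. A fuller economic plan may settle this. But the article states a positive list of costs, and medication bought by MHCP outside the study supply is not on it.

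It is also fair that pooling MHCP drug costs with quitline costs would blur the viewpoint. The two are named as alternatives, and nothing says that MHCP funds the quitline. Quitline use would come from a survey planned with 40% nonresponse, and the article defines counseling only as at least one call or visit, with no stated measure of call volume.

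**Conclusion.** The concern holds for the medical-assistance adopter. For that adopter the listed costs leave out MHCP-paid cessation medication, which is available in both arms and may be prompted by referral in the proactive arm. The ICER as listed is program cost per added quitter. It does not measure what that payer would spend, net, by moving from usual care to the proactive program.

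The only size that can be given is the conversion rate: $286 per added quitter for each $10 per participant of net omitted cost at a 3.5-point difference, $250 at 4 points. This assumes that the true difference equals one of the two planning values. The dollar and percentage shifts in the illustration rest on assumed costs and uptake.

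A reader might conclude that the plan makes the intervention look too cheap, or too expensive. The article supports neither. Displaced NRT would make the listed-items ICER too high for this payer, induced prescribing would make it too low, and the article gives no data on which dominates. The primary outcome, its test and the sample size are unaffected.

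**What to change.** 1. Keep the present ICER and label it as program cost per added quitter, stating that no treatment bought outside the program is counted in either arm.
2. Add a medical-assistance-payer ICER, at least as a prespecified sensitivity analysis. It should add MHCP-paid cessation medication over the 12 months after randomisation to the costs of both arms. Use the pharmacy claims already being extracted, priced at paid amounts or at stated unit costs, and carry these costs through the planned bootstrap and probabilistic sensitivity analyses.
3. Do not put quitline costs into the payer ICER. If a quitline adopter is of interest, report a separate version and state its limits: survey nonresponse and no stated measure of call volume.

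The cost is a few unit costs and one more ICER. The article lists prescription rates, number and duration from claims but not paid amounts, so either that field must be requested or unit prices applied. The medication costs do not depend on survey response, and no new participant contact is needed.

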### Sample size and power analysis

The power analysis assumes independent samples in the two groups within strata and considers a type one error rate of 0.05 for analysis of the primary outcome, six-month prolonged abstinence. The goal sample size for this study is N = 2500 (1250 per group), which accounts for a 40% nonresponse rate to the follow-up survey to ensure that we have observed smoking status outcome data on 1500 respondents (750 per group). The anticipated six-month prolonged smoking abstinence rate in the usual care arm is between 2% to 5%. This sample size provides over 85% power to detect intervention effects if the intervention raises abstinence rates by 4% and provides approximately 80% power or greater to detect differences if the intervention raises quit rates by 3.5%. The difference this study is powered to detect is of the same relative order of magnitude as those in prior smoking cessation clinical trials (e.g. odds ratios of 1.5 to 2.0) [49].

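### The plan bootstraps a standard error for an ICER whose denominator can be zero or negative, so that standard error is not finite and simple percentile limits can lose their meaning

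*Protocol article*

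**What the plan says.** Determining cost-effectiveness is listed among the primary objectives in the Abstract (Methods/Design). The section Cost-effectiveness analysis defines the ICER as the expected cost difference between arms divided by the corresponding expected outcome difference, and then states: "We will use bootstrap methods to estimate standard errors and confidence intervals for these cost-effectiveness measures". It presents the bootstrap as a convenient way to carry the correlation of cost and outcome into the standard errors. The analysis is to be repeated under each of the nonresponse sensitivity analyses.

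The same section says that "costs are measured by the per participant budgetary costs" incurred in delivering the interventions, and lists only programme costs. It describes the outcome first as a difference in prolonged abstinence and then as an outcome of interest, "namely the numbers of individuals achieving prolonged abstinence at 12 months". A later sentence says that total costs stay fixed across the sensitivity analyses.

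The section Sample size and power analysis plans for "observed smoking status outcome data on 1500 respondents (750 per group"), expects usual-care abstinence of 2% to 5%, and gives power for gains of 3.5 and 4 points. It compares these gains with odds ratios of 1.5 to 2.0 from earlier trials.

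**The concern.** A ratio behaves badly when its denominator may be near zero. A replicate with equal abstinence in both arms has no ICER. A replicate one abstainer away from equality has an enormous one, of either sign. A standard error over such replicates describes those few extreme values and not the precision of the estimate.

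Intervals have a separate, ordering problem. With a positive cost difference, a negative ratio means more costly and less effective, which is worse than any positive price. A plain numerical sort places it at the favourable end.

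What is at stake is the precision reported for one of the stated primary objectives, and most of all when the observed effect is modest.

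**Working it through.** **Inputs.** From Sample size and power analysis: 750 observed outcomes per arm, usual care 2% to 5%, gains of 3.5 and 4 points, odds ratios 1.5 and 2.0, and "type one error rate of 0.05" (taken as two-sided). The article gives no cost, so a fixed difference of $100 per person is *assumed*. Every dollar figure scales in proportion to it.

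**The plan's own figures.** 1500 / 0.60 = 2500, as stated. Power at +4 points is 97.7% (usual care 2%) to 86.0% (5%), which agrees with the article. Power at +3.5 points is 94.7% to 77.1%, which agrees except slightly at the 5% end. The article gives no figure for the ICER's precision.

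**Step 1: chance of a non-positive denominator.** SE(d) = √[p₁(1−p₁)/750 + p₂(1−p₂)/750]. If the observed difference equals the true one, the share of replicates at or below zero is Φ(−d/SE).

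**Step 2: how often this spoils a percentile interval.** The bootstrap is centred on the *observed* difference. More than 2.5% of replicates are non-positive when observed d/SE falls below about 1.96, which has probability Φ(1.96 − d/SE). This was checked by simulating 4,000 trials per row with 2,000 bootstrap draws each.

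| Usual care vs intervention | SE, points | d/SE | Step 1 | Step 2, formula | Step 2, simulated |
|---|---|---|---|---|---|
| 5% vs 8.5% | 1.29 | 2.71 | 0.34% | 22.7% | 23% |
| 5% vs 9% | 1.31 | 3.04 | 0.12% | 13.9% | 15% |
| 2% vs 5.5% | 0.98 | 3.58 | 0.02% | 5.2% | 5% |
| 2% vs 6% | 1.01 | 3.97 | 0.004% | 2.2% | 2% |
| 5% vs 7.3% (OR 1.5) | 1.24 | 1.87 | 3.1% | 53.6% | 55% |
| 2% vs 3.0% (OR 1.5) | 0.80 | 1.21 | 11.4% | 77.4% | 80% |
| 5% vs 9.5% (OR 2.0) | 1.33 | 3.39 | 0.04% | 7.7% | 8% |
| 2% vs 3.9% (OR 2.0) | 0.87 | 2.20 | 1.4% | 40.6% | 43% |

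**Step 3: the standard error at 5% vs 8.5%.** Take 38 and 64 abstainers of 750. The ratio is 100 × 750 / 26 = $2,885. The exact binomial distribution puts 0.11% of replicates at exactly zero, about one per 1,000 draws, and there the ratio is undefined. A finite figure appears only if these are discarded. It is then $4,669, larger than the ratio itself. Differences of plus or minus one abstainer are 0.23% of replicates, each with a ratio of ±$75,000. They contribute about 0.0023 × 75,000² ≈ 13 million to a variance of 4,669² ≈ 21.8 million, which is more than half. The figure therefore depends on how many such draws occur: ten runs of 1,000 draws gave $2,500 to $5,726, and ten runs of 2,000 gave $4,001 to $5,341. At 2% vs 5.5% the standard error is about $1,700, below the ratio, but zero replicates still occur.

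**Step 4: the interval.** At 5% vs 8.5%, with the observed difference equal to the true one, percentile limits are stable at about $1,630 to $9,375. Fieller limits with a fixed cost are 100 / (0.035 ± 1.96 × 0.0129), about $1,660 to $10,300, so there is no difficulty there. At 5% vs 7%, about 5.8% of replicates are non-positive and the percentile limits run from −$18,750 to $37,500. In correct order those replicates lie beyond every positive price, so the upper limit is unbounded. The lower limit is about 100 / (0.02 + 1.96 × 0.01225) ≈ $2,270. The −$18,750 is an artefact of sorting.

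**Step 5: net benefit.** NB(λ) = λ(O_T − O_UC) − (C_T − C_UC) is linear, so its standard error exists at any effect. For an assumed λ of $5,000 per added abstainer at 5% vs 8.5%: 5,000 × 0.035 − 100 = $75, SE 5,000 × 0.0129 ≈ $65, and 95% limits about −$52 to $202.

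**The case against.** The article does not say percentile limits. The interval type, the handling of non-positive replicates, net benefit and acceptability curves may all be in an analysis plan that is not shown, and their absence is not held against the article. This stands for the interval, so that part is conditional. It does not cover the standard error, which the article commits to in so many words.

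At the powered effects few replicates are non-positive if the observed difference equals the true one (at most 0.34%). That is correct but incomplete. The observed difference varies from trial to trial, and Step 2 shows what follows.

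A reader might infer that negative ratios mix harm with savings. The documents do not support that. Only the costs of delivering the intervention are counted, so the cost difference is almost surely positive and a negative ratio means less effective and more costly. What remains is the ordering problem.

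A reader might also infer that total costs for all 1,250 per arm are divided by abstainers counted only in the 750 respondents, inflating the ICER by 1250/750 = 1.67. Nothing in the text says so. Per-participant costs and expected differences allow a per-person reading in which no inflation arises. The 750 belongs to the power calculation, the article assigns no 1,250 to costs, and the sentence on total costs says only that missing-data assumptions alter effects and not costs.

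**Conclusion.** The point holds for the standard error: the article plans one for a quantity that has none. Near the upper end of the expected usual-care rate, the value a program would print exceeds the ratio and is unstable at ordinary numbers of draws. For intervals the point is conditional on simple percentile limits. These would fail in roughly 5% to 23% of trials at a true gain of 3.5 points, 2% to 15% at 4 points, and 54% to 80% at an odds ratio of 1.5.

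The results assume 750 informative outcomes per arm and simple binomial sampling without strata, and the dollar figures assume a fixed $100 cost difference. The frequencies in the table need only a positive cost difference and do not depend on its size. The ICER point estimate, the primary abstinence test and trial conduct are unaffected.

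On the base for cost and effect there is only a wording inconsistency: per-person against total costs, and a difference in abstinence against a count of abstainers. No bias is shown.

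**What to change.** - Remove the standard error of the ICER.
- Report the ICER as a point estimate, with Fieller limits or bootstrap limits ordered so that more costly, less effective replicates rank beyond all positive prices. Where no finite limit exists, say so.
- Express uncertainty through incremental net benefit with bootstrap intervals over a stated range of willingness to pay per additional abstainer, plus the acceptability curve. Do the same in each nonresponse sensitivity analysis.
- In one sentence, define cost as the mean per randomised person and effect as the difference in abstinence proportion on the same base.

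The cost is a few lines in the analysis plan. The same bootstrap draws serve, and no new data are needed.
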